## Abstract

**Background:**

Although Primary Health Care (PHC) Teams are used to deal with prevention and treatment of sanitary problems in adults with chronic diseases, they usually have a lack of experience in development of psychotherapeutic interventions. However, these interventions are the ones that achieve better results to reduce symptomatology and improve emotional state of caregivers.

The study aims to evaluate the effectiveness of an intervention of psychotherapy in improving the mental health and Quality of life of caregivers. This intervention is based on theoretical approaches to care adjusted to cognitive theory, in order to be applied in primary health care centres.

**Methods/Design:**

This is multicentre clinical trials study, randomized in two parallel groups, carry out in two PHC, Study population: 150 caregivers will be included by consecutive sampling and they will be randomized the half to experimental group and the other half to control group. They provide mostly all the assistance to care-dependent familiars receiving attention in PHC Centers.

Measurements: Each caregiver will be evaluated on a personal interview. The caregivers' assessment protocol: 1) Assessment of different socio-demographic related to care, and caregiver's personal situation. 2)Care-dependent individuals will also be assessed by Barthel Index and Pfeiffer Questionnaire (SPMSQ). 3)Change in caregivers will be the principal measure: family function (Family APGAR Questionnaire), burden short questionnaire (Short Zarit Burden Interview), quality of life (Ruiz & Baca: 1993 Questionnaire), the Duke-UNK Functional Social Support Questionnaire, the General Health Questionnaire-12, and changes in Dysfunctional Thoughts about caring. 4) Intervention implementation measures will also be assessed.

Intervention: A psychotherapeutic intervention will be 8 sessions of 90 minutes in groups. This intervention has been initially developed for family caregivers of patients with dementia.

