### Study population

The study will be carried out at the Primary Health Care System in urban areas. The study subjects will be adults both male and female living near two health centers in the city of Salamanca (La Alamedilla, Miguel Armijo), an estimated population of 42.000 residents. The health care professionals of both centers will offer the caregivers of dependent relatives the opportunity to participate on the study. Once the informed consent is signed, a researcher will complete the preintervention assessment by means of an individual interview.

The sample size is expected to reveal a difference of or superior to 12 units on the Ruiz-Baca's quality of life questionnaires between the intervention group and its control. With an estimated alpha risk 0.05 and a beta risk 0.20 in a bilateral contrast, 73 subjects are required in the first group and 73 in the second one. The common standard deviation assumed is 25.7 from a previous study.

Through consecutive sampling, 150 caregivers will be included, who are responsible for almost all the care given to dependent and ill relatives who receive health care in the centers. One half will be randomly assigned to the trial group and the other half to the control group in a waiting list format. Those in the control group will be offered to participate in the therapy sessions, but only once the intervention and final assessment of the first group have been completed. Those in the intervention group will be divided into groups of 8 and 12 subjects for the group sessions.

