#### 2. Result Variables

Variables will be assessed before the intervention and after six months of the first assessment. Questionnaires in Spanish will be used as determined by the validations performed in the Primary Health Care System. The following questionnaires are to be used:

a) Family functionality perceived by the caregiver was evaluated with the Family APGAR Questionnaire validated in Spain [15]. This questionnaire rates satisfaction with family relations and distinguish five components of the family function: adaptability, partnership, growth, affection and resolve. It consists of the five questions, with three possible answers: 0 ("hardly ever"), 1 ("sometimes"), 2 ("always"). The total score range varies from 0 to 10, meaning the higher total score, the better family functioning. A global score of 7 points or more indicates family functionality, while a score of less than 7 points indicates family dysfunction. The internal consistency (Cronbach's alpha) of this questionnaire in this study was 0.77.

b)The Short Zarit Interview used in palliative care cases to determine the family giving up has an S of 100%, Sp 90.5%, PPV 95.45%, and NPV 100% in defining caregivers' burden in primary care [16].

c) Quality of life was evaluated with Ruiz and Baca's Questionnaire (1993) [17]. This is made up of 39 items each with a Likert-type five-point scale comprising four dimensions: social support, general satisfaction, physical/mental well-being, work overload and free time. This study gave an internal consistency index (Cronbach's alpha) of 0.94.

d) Social support: in order to measure caregivers' perception of the amount and type of personal social support they receive, the 11-item version [18] of the Duke-UNC Functional Social Support Questionnaire [19] was used. Response options to the items (for example, ''I get love and affection'') are on a 5-point scale ranging from 1 (''much less than I would like'') to 5 (''as much as I would like''). The scale had good internal consistency (Cronbach's a = 0.82).

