### Statistical analysis

Data input will be made using the Teleform system (Autonomy Cardiff Vista, California, USA), with a questionnaire previously designed for the project, and exporting the data to the SPSS version 15.0 statistical package (SPSS Inc., Chicago, Illinois, USA) for posterior analysis.

A first descriptive analysis of the socio-demographic characteristics of the study groups will be made. The data will be presented with the mean and standard deviation in the case of quantitative variables, and as frequency distributions for qualitative variables. The Pearson chi-squared test will be used to analyze associations between qualitative variables. The Student t-test for independent samples will be used to compare the means for the two groups. In turn, the analysis of repeated measures will be based on the McNemar test for qualitative data and the Student t-test for paired data in application to quantitative data.

In order to describe the characteristics and intensity of the caregivers' analyzed variables, the sum of the grades as well as its mean will be used, so as to compare the range of grades and make their interpretation easier. Analyzing the impact of the intervention will be carried out through intent to treat analysis.

The contrasting hypothesis will establish an alpha risk factor of 0.05 as the limit of statistical significance.

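### Six questionnaires share principal status, but the trial is sized on one of them and no rule says which decides effectiveness

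*Protocol article*

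**What the plan says.** The Methods/Design paragraph of the abstract sets out four blocks of assessment. The third reads "Change in caregivers will be the principal measure: family function (Family APGAR Questionnaire), burden short questionnaire (Short Zarit Burden Interview), quality of life", and its list ends with the Duke "Functional Social Support Questionnaire, the General Health Questionnaire-12, and changes in Dysfunctional Thoughts about caring". That makes six questionnaires: Family APGAR, Short Zarit, Ruiz-Baca, Duke-UNC, GHQ-12 and Dysfunctional Thoughts.

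The Result Variables section gives the same six, lettered a) to f), under one timing statement: "Variables will be assessed before the intervention and after six months of the first assessment". None is called primary and none secondary.

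The Study population section sizes the trial on one of the six: "The sample size is expected to reveal a difference of or superior to 12 units on the Ruiz-Baca's quality of life questionnaires". The other inputs are "With an estimated alpha risk 0.05 and a beta risk 0.20 in a bilateral contrast" and "The common standard deviation assumed is 25.7 from a previous study", and the result is "73 subjects are required in the first group and 73 in the second one". Planned enrolment is 150, half to each group.

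The Statistical analysis section names the independent-samples t-test for comparing the two groups and closes with one limit: "The contrasting hypothesis will establish an alpha risk factor of 0.05 as the limit of statistical significance". It gives no hierarchy, no division of alpha and no statement of which result or results would count as effectiveness.

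**The concern.** The sizing paragraph treats the trial as having one deciding outcome. The abstract gives six outcomes the same standing. Nothing else in the article settles which reading governs. The sizing paragraph does not call Ruiz-Baca primary, the stated aim covers both mental health and quality of life, and the second objective targets dysfunctional beliefs. At least three of the six scales (Ruiz-Baca, GHQ-12 and Dysfunctional Thoughts) can each claim to answer a stated objective.

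At stake is the meaning of a positive result. The Discussion says that an effective intervention could be introduced in general care programs. The Limitations section says that the questionnaires have not proved sensitive enough to change, so mixed results across the six scales are foreseeable. With mixed results and no ranking, the article does not say whether the trial succeeded, and neither the 5% nor the 20% error rate can be attached to the answer.

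**Working it through.** **Step 1: reproduce the plan's own figure.** Inputs from Study population: difference 12, SD 25.7, two-sided alpha 0.05, power 0.80, equal groups.

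n per group = 2 × [SD × (z₀.₉₇₅ + z₀.₈₀) / difference]² = 2 × [25.7 × (1.960 + 0.842) / 12]² = 72.001, rounded up to 73.

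The calculation based on the t distribution gives 72.97, also 73. The stated figure reproduces, so the sizing is correct for one outcome tested at 0.05. At the planned 75 per group, power is 81.6% (normal) or 81.1% (t).

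**Step 2: error rate if any one of six scales sufficed.** This success rule is an assumption made to size the problem; the article does not state it. With six independent null outcomes:

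- At least one significant difference in either direction: 1 − 0.95⁶ = 0.265.
- At least one significant difference favouring the intervention: 1 − 0.975⁶ = 0.141.

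The six scales are answered by the same caregivers, so correlation is expected, but the article gives none. For a common correlation ρ between test statistics (each scale oriented so that positive is favourable), with c = 1.96, the probability of no rejection in either direction is

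∫ φ(u) [Φ((c − √ρ·u)/√(1−ρ)) − Φ((−c − √ρ·u)/√(1−ρ))]⁶ du.

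For favourable results only, the bracket becomes Φ((c − √ρ·u)/√(1−ρ)). One minus each integral gives:

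| Assumed ρ | Either direction (nominal 5%) | Favouring the intervention (nominal 2.5%) |
|---|---|---|
| 0 | 26.5% | 14.1% |
| 0.3 | 24.1% | 12.2% |
| 0.5 | 20.7% | 10.4% |
| 0.7 | 16.4% | 8.2% |
| 0.8 | 13.9% | 6.9% |
| 0.9 | 10.8% | 5.4% |

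Even at 0.9 both columns are about twice nominal.

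**Step 3: the other possible success rules.**

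- *Ruiz-Baca alone decides.* Alpha is 5% and power about 81% at 75 per group. Both stated figures hold.
- *All six must be significant.* There is no inflation of alpha. The chance of success cannot exceed the power for Ruiz-Baca, and the article gives no power for the other five, so the 80% does not describe the trial.
- *Six co-equal outcomes with Bonferroni.* Each is tested at 0.05/6 = 0.0083. Power for the 12-unit difference at 75 per group falls to 57% (t) or 59% (normal). Restoring 80% takes 112 (normal) or 113 (t) per group, up to 2 × 113 = 226 caregivers against the planned 150.

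Only the first rule fits the existing sample size with both error rates as stated.

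**The case against.** The strongest reply is that principal in the abstract describes a block, not a set of six co-primary endpoints. The grammatical subject is singular (change in caregivers), and the sentence sets that block apart from socio-demographic data, the dependent person's status and the implementation measures. The body heading is simply Result Variables, the closing sentence of the analysis section speaks of one hypothesis, and the sample size rests on Ruiz-Baca alone. On that reading Ruiz-Baca is already the working primary outcome and the abstract is loosely worded. This reading is possible, and it supports the fix below. It does not remove the point, because no sentence says that Ruiz-Baca decides.

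A second reply is that multiplicity detail belongs in a fuller protocol or analysis plan that is not shown. That stands for the handling of secondary outcomes, so no particular adjustment is asked for. It does not cover a mismatch that the article itself creates between its abstract and its sample size.

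A reader might go further and infer that the trial's false-positive risk for the claim that the intervention works is 16% to 26%. The article does not support that. Those figures count differences in either direction, including apparent harm; they require a rule that any one scale suffices, which the article does not state; and they stop at an assumed correlation of 0.7. A reader might also count the four Ruiz-Baca dimensions as further tests, or suppose an intention to headline the best scale. The dimensions are only described, the analysis section plans no tests of them, and nothing in the article speaks to such an intention.

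**Conclusion.** The point holds as an inconsistency over which outcome is decisive. The article gives six questionnaires equal standing, computes power for one and states one 0.05 limit without a success rule. Its 5% alpha and 80% power both apply to a claim of effectiveness only if Ruiz-Baca alone decides.

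The size is conditional. If any one significant scale were taken as effectiveness, the chance of at least one false positive favouring the intervention would run from about 14% (independent scales) to 7% (correlation 0.8), against 2.5%. In either direction it would run from 26.5% to 14%, against 5%. These figures assume that all six null hypotheses are true and that the correlations are equal, and the correlations are assumed values. The 73 per group is not in dispute.

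**What to change.** - In Study population and Result Variables, name the Ruiz-Baca total score at six months, intervention against control, as the single primary outcome, tested at two-sided 0.05. This matches the existing sample size and keeps about 81% power at 75 per group, taking the assumed SD of 25.7 to apply to that score.
- Label the other five questionnaires as secondary. Report them as supportive with confidence intervals, or under one prespecified multiplicity procedure of the sponsor's choice.
- Reword the abstract so that principal measure refers to the Ruiz-Baca score only.
- Make and date the change before any between-group outcome data are seen. The Result Variables section reports internal consistency for some scales in terms that could mean that study data already existed, so the date should be documented.

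The cost is a change of wording and no additional caregivers. The one downside is that a lone significant secondary scale could no longer be claimed as proof of effectiveness.

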**Discussion:**

Psychotherapeutic interventions have been proved to obtain better results to reduce symptomatology and improve emotional state of caregivers. Moreover, this intervention has been proved to be effective in a different setting other than PHC, and was developed by professionals of Mental Health. If we found that this intervention is effective in PHC and with our professionals, it would be an important instrument to offer to caregivers of care-dependent patients.

**Trial Registration:**

ClinicalTrials.gov Identifier NCT01177696

## Background

Nowadays, family caregivers are one of the most important resources in the care provided to dependent patients. In numerous occasions the responsibility they face causes physical, mental and economic alterations that might lead to the resignation of the family caregiver, as well as to the deterioration of the quality of life and the institutionalization of the patient under care [1-3].

The great number of occurrences of mental health disorders caused by the care given to the dependent population is corroborated by several studies affirming that the restriction of social activities, insomnia, psychological discomfort, despair, excess, stress, physical problems, difficulties in the work and professional sphere, emotional disruption (anxiety, depression), reduction of leisure time [4] and feelings of discomfort regarding life in general, are just some examples that indirectly deteriorate the quality of life of the caregiver, the patient and the family unit [5,6]. An appropriate service to the caregiver, working alongside the social services and establishing measures to combine family and professional life may contribute to prevent or palliate the so-called "ill caregiver syndrome", increase his or her self-esteem and quality of life, improve the care to a dependent person and avoid his or her institutionalization [3]. Several different educational programs have been developed with data indicating a significant increase of the caregiver's knowledge on the development of the relative's disease and on his or her competence. However, their effectiveness to reduce the caregiver's discomfort has not been proven yet [7]. In fact, in some cases this type of programs causes tension, rather than reducing it, but usually include information about problems that do not affect the patient under care, anticipating future problematic situations that might never occur. Moreover, it has been verified that a better knowledge about the disease of the dependent patient does not correlate with a lesser emotional discomfort on the part of the caregiver [8,9]. This reveals the necessity to evaluate the effectiveness of non-pharmacological therapies.

Psychotherapeutic interventions achieve best results in reducing the symptomatology and improving the emotional state of the caregivers [7]. However, in order to develop those intervention programs, which alleviate the burden of the caregiver, they have to be designed from a multi-dimensional and multi-professional perspective [10]. In addition, the intervention must be carried out by well-trained professionals with the capacity to face, control and solve their emotional problems.

For a long time, Primary Health Care Teams have been dealing with the prevention and treatment of health problems in adults with chronic diseases. There are the professionals who offer health care to dependent patients as well as to their caregivers. Although their necessities are covered by the Primary Health System, it is an enormously difficult task, mainly because health care professionals lack the appropriate training to perform basic duties needed in this field. According to a study carried out in Primary Health Care System [11], three out of 4 health care professionals feel competent to attend demands related with routine care tasks; just 5.5 out of 10 feel competent in advising on problematic behavior and problematic situations related to health care, whereas only 3 out of 10 feel qualified to offer some guidance on the consequences of such care. A vast majority of professionals believe that there is a need to train the caregivers on psychosocial and behavioral aspects so as to more accurately assist them on their necessities. Given into account that 7 out of 10 claim not to have received any kind of training on this matter, it seems logic to assume that the majority of the necessities put forward directly or indirectly by the caregivers are at present not been dealt with. Thus, it is essential to invest on professional training on a field with a great impact on the personal, social and political levels.

By means of a standard psychotherapeutic intervention, Losada et al.[12] achieved to modify a variety of problematic behaviors in groups of family caregivers of patients suffering from dementia.

This essay attempts to analyze a psychotherapeutic intervention from a comprehensive perspective similar to that of Losada with caregivers of patients suffering from different pathologies in the primary health care context.

The following objectives have been established:

1.- Designing and assessing a psychotherapeutic intervention strategy in the Primary Health Care System to efficiently work on the mental health and the quality of life of the family caregivers of dependent patients.

2.- Assessing a cognitive-behavioral intervention, which is to be applied on Primary Health Care Centers, in order to modify the dysfunctional beliefs so as to appropriately deal with the care given, based on the principles of the cognitive theory.

## Methods/Design

### Design

This is a multicentered, randomized, controlled, clinical trial to assess the effectiveness of a group intervention on the family caregivers of dependent patients.

### Study population

The study will be carried out at the Primary Health Care System in urban areas. The study subjects will be adults both male and female living near two health centers in the city of Salamanca (La Alamedilla, Miguel Armijo), an estimated population of 42.000 residents. The health care professionals of both centers will offer the caregivers of dependent relatives the opportunity to participate on the study. Once the informed consent is signed, a researcher will complete the preintervention assessment by means of an individual interview.

The sample size is expected to reveal a difference of or superior to 12 units on the Ruiz-Baca's quality of life questionnaires between the intervention group and its control. With an estimated alpha risk 0.05 and a beta risk 0.20 in a bilateral contrast, 73 subjects are required in the first group and 73 in the second one. The common standard deviation assumed is 25.7 from a previous study.

Through consecutive sampling, 150 caregivers will be included, who are responsible for almost all the care given to dependent and ill relatives who receive health care in the centers. One half will be randomly assigned to the trial group and the other half to the control group in a waiting list format. Those in the control group will be offered to participate in the therapy sessions, but only once the intervention and final assessment of the first group have been completed. Those in the intervention group will be divided into groups of 8 and 12 subjects for the group sessions.

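### The stated between-arm t-test ignores centre in a two-centre trial; a model with centre and baseline score would gain a little precision at almost no cost

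*Protocol article*

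**What the plan says.** The abstract of the protocol article describes the design thus: "This is multicentre clinical trials study, randomized in two parallel groups, carry out in two PHC". The Study population section names the two centres, says that the professionals of both will invite caregivers, and sets the total: "Through consecutive sampling, 150 caregivers will be included". On allocation the same section says: "One half will be randomly assigned to the trial group and the other half to the control group in a waiting list format". That sentence fixes a 1:1 ratio. It does not say whether the list was built separately for each centre.

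The sample size is set to detect "a difference of or superior to 12 units on the Ruiz-Baca's quality of life questionnaires between the intervention group and its control". The error rates are given as follows: "With an estimated alpha risk 0.05 and a beta risk 0.20 in a bilateral contrast". The spread is also given: "The common standard deviation assumed is 25.7 from a previous study". The result is 73 caregivers per group.

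The Statistical analysis section names one comparison of group means: "The Student t-test for independent samples will be used to compare the means for the two groups". It adds paired tests for change within a group and an intention-to-treat principle. No centre term and no adjusted model appear in the article. The Result Variables section has each questionnaire completed before the intervention and again six months after the first assessment, and the abstract makes change in caregivers the principal measure.

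**The concern.** The two centres have their own populations and staff, so centre may plausibly predict quality of life, burden and perceived support. The Discussion also makes reproducibility across centres part of the trial's purpose. An independent-samples t-test leaves any difference between centres in the residual variation.

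What this costs depends on how the list was made, and the article does not say:

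- **List not stratified by centre.** The test is unbiased and keeps its 5% error rate, but its standard error is larger than that of a test that removes the centre difference.
- **List stratified by centre.** The arms are balanced on centre by design, but the t-test does not use that balance. Its standard error is too large and it rejects slightly less often than 5% under the null.

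A centre term answers both cases. What is at stake is a little power in a trial that plans 75 per arm against 73 required.

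**Working it through.** **Inputs from the protocol article:** target difference 12; SD 25.7; two-sided alpha 0.05; power 0.80; 150 caregivers in two halves, so 75 per arm; two centres.

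**Assumptions, because the documents give no figure:** the centres contribute equally (75 each); the SD of 25.7 is the total SD, including any centre difference; the gap in mean score between centres is g = 0, 0.2, 0.3 or 0.5 SD, that is 0, 5.14, 7.71 or 12.85 units.

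**Step 1. The plan's own figure.** n per arm = 2 × [25.7 × (1.960 + 0.842) / 12]² = 72.001, rounded up to 73. This agrees with the article. A noncentral-t check gives 80.0% power at 73 per arm and 81.1% at 75.

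**Step 2. Variance due to centre.** With equal centres, the share of variance explained by centre is g²/4 (g in SD units). The within-centre SD is 25.7 × √(1 − g²/4), and the standard error of the arm difference is that SD × √(2/75). Without a centre term it is 25.7 × √(2/75) = 4.20.

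**Step 3. Power and error rate.** Power uses the noncentral t with 148 degrees of freedom without a centre term and 147 with it. The last column is the true two-sided error of the plain t-test if allocation was stratified by centre: 2 × [1 − Φ(1.960 / √(1 − g²/4))].

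| Gap g (SD) | Variance due to centre | SE with centre term | Power, plain t-test | Power, centre term | Error rate of plain t-test if stratified |
|---|---|---|---|---|---|
| 0 | 0% | 4.20 | 81.1% | 81.1% | 5.0% |
| 0.2 | 1.0% | 4.18 | 81.1% | 81.5% | 4.9% |
| 0.3 | 2.25% | 4.15 | 81.1% | 81.9% | 4.7% |
| 0.5 | 6.25% | 4.06 | 81.1% | 83.5% | 4.3% |

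**Step 4. Is chance imbalance a further cost?** If the list was not stratified, the number from one centre in an arm is hypergeometric (75 drawn from 150, of whom 75 belong to that centre). The arm difference in centre share then has an SD of 0.082. At g = 0.5 SD the resulting shift in the estimate has an SD of 0.082 × 12.85 = 1.05 units. Adding this to the within-centre standard error gives √(4.06² + 1.05²) = 4.20, which is the plain t-test's standard error from Step 2. The imbalance is therefore already in the unadjusted standard error. It is the same cost as the lost precision and must not be counted twice.

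The gain from the pre-intervention score is not computed, because the documents give no correlation between the two assessments.

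**The case against.** The strongest reply is that nothing here is wrong. The unadjusted t-test is a legitimate primary comparison, the 73 per arm reproduces, and covariates are often left to an analysis plan that is not shown. The gap is assumed. Its top value, 12.85 units, exceeds the 12-unit treatment effect, and both centres are urban practices in one city with the same assessors for both arms. At 0.2 to 0.3 SD the gain is only 0.4 to 0.8 percentage points of power.

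Most of this stands, and it sets the size of the point. It does not remove it: the article names a specific test, and that test omits a factor known at entry.

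Three stronger readings are tempting, and the documents do not support them.

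- **That the 150 were randomised as one pool.** Under that assumption there would be a 19% chance of the arms differing by 10 percentage points or more in centre share. But the sentence on allocation gives only the ratio, and a condensed article commonly leaves the structure of the list to the full protocol. No claim is made here that allocation was unstratified.
- **That the effect estimate is biased or the test invalid.** It is unbiased on average, and its error rate is 5% or slightly below.
- **That the trial is too small without a centre term.** Power at 75 per arm is 81.1% with the plain t-test.

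A further objection is that adjusting for centre alone would leave out the baseline value of the outcome, although change is the principal measure. That is right, so the fix includes it.

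**Conclusion.** The point holds as a small improvement to the analysis. The stated between-arm test ignores centre in a two-centre trial. The price is between nothing and about 2.4 percentage points of power for gaps up to 0.5 SD, or an error rate between 5.0% and 4.3% if allocation was stratified.

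These figures rest on equal centres, 25.7 as the total SD, 75 analysed per arm, and assumed gaps that the documents neither give nor rule out. The conclusion does not depend on how the list was made: a centre term is suitable in either case. The stated sample size is unaffected.

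**What to change.** In the Statistical analysis section, replace the independent-samples t-test for the between-arm comparison of scores by a linear model. The outcome is the six-month score. The fixed terms are arm, centre and the pre-intervention score of the same questionnaire. Report the arm coefficient with its 95% confidence interval, under the intention-to-treat principle already stated. Fix this before the outcome data are examined, so that the adjustment cannot be seen as chosen after the result.

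The cost is one degree of freedom for each of the two added terms, out of 148. At zero gap the centre term changes power by less than 0.01 percentage points. The model runs in the named statistical package and needs no further data, staff or caregivers, since centre and the pre-intervention scores are already collected.

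### Treatment is delivered in therapy groups in one arm only, but the sample size and the planned t-test assume independent caregivers; any positive within-group correlation makes the t-test too liberal and lowers the power of a valid analysis

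*Protocol article*

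**What the plan says.** All the relevant statements are in the protocol article.

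- **Allocation** (Study population): "Through consecutive sampling, 150 caregivers will be included", and caregivers are allocated individually and 1:1: "One half will be randomly assigned to the trial group and the other half to the control group in a waiting list format". Controls are offered therapy only after the final assessment, so they share no therapy group before the outcome is measured.
- **Delivery** (Study population): "Those in the intervention group will be divided into groups of 8 and 12 subjects for the group sessions". This is read here as group sizes from 8 to 12.
- **Sample size** (Study population): "The sample size is expected to reveal a difference of or superior to 12 units on the Ruiz-Baca's quality of life questionnaires". For a two-sided alpha of 0.05, power of 80% and an SD of 25.7 in both arms, the stated result is: "73 subjects are required in the first group and 73 in the second one". No ICC, design effect or group size enters.
- **Analysis** (Statistical analysis): "The Student t-test for independent samples will be used to compare the means for the two groups". This is the only between-arm comparison of means that is named. Intention to treat is stated, but no term for therapy group appears.

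The Limitations section concedes that the sample may prove too small, but does not mention clustering.

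**The concern.** Members of one therapy group share the therapists, the discussion and each other's company over eight sessions. Their outcomes may therefore resemble each other more than those of caregivers in different groups. The waiting-list arm has no such structure, so the design is partially nested: clustered in one arm and independent in the other.

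If group effects vary, the variance of the intervention mean is inflated by 1 + (m − 1) × ICC, where m is the group size. The ordinary t-test does not see this inflation. Its standard error is then too small, its intervals are too narrow, and it rejects too often when the average effect is zero. An analysis that does account for the groups has fewer effective observations, and few degrees of freedom from 6 to 9 groups, so its power is below what the sample-size paragraph implies. The article's Discussion envisages introducing the programme into general care if it proves effective, so a liberal test matters.

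**Working it through.** **Inputs from the document:** difference 12, SD 25.7, two-sided alpha 0.05, power 0.80, 73 required and 75 enrolled per arm (150/2), group size 8 to 12. **Assumed:** the ICC, which the document does not give; total SD of 25.7 in both arms; equal group sizes; no dropout.

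**Step 1: the plan's own figure.** n per arm = 2 × (1.960 + 0.842)² × 25.7² / 12² = 72.0 by the normal formula, and 72.97 by the noncentral t. Both round up to 73, so the figure is correct under independence. At 75 per arm, power under independence is 0.816 (z) or 0.811 (t).

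**Step 2: number of groups.** 75/12 = 6.25 and 75/8 = 9.4, so about 6 to 9.

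**Step 3: formulas with grouping.**
- Design effect: DE = 1 + (m − 1) × ICC.
- SE assumed by the t-test = 25.7 × √(2/75) = 4.197.
- True SE = 25.7 × √((DE + 1)/75).
- Type I error of the plain t-test ≈ 2 × [1 − Φ(1.96 × SE assumed / SE true)].
- Adjusted power, z approximation = Φ(12 / SE true − 1.96).
- Adjusted power, small-sample: noncentral t with Satterthwaite degrees of freedom, using k − 1 for the intervention mean (k = 75/m groups) and 74 for the control mean.
- n per arm for 80% (z) = 25.7² × (1 + DE) × (1.960 + 0.842)² / 12².

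**Step 4: one case in full, m = 10 and ICC 0.05.** DE = 1 + 9 × 0.05 = 1.45. True SE = 25.7 × √(2.45/75) = 4.645, which is 1.107 times the assumed SE. Type I error = 2 × [1 − Φ(1.771)] = 0.077. Power by z = Φ(2.583 − 1.96) = 0.73. With 17.8 degrees of freedom (critical value 2.103) it is 0.68.

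**Step 5: the range, 75 per arm.** Each pair runs from m = 8 to m = 12.

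| Assumed ICC | Plain t-test type I error | Adjusted power, z | Adjusted power, small-sample df | Plain t-test rejection rate at 12 units | n per arm for 80% (z) |
|---|---|---|---|---|---|
| 0 | 0.050 | 0.816 | 0.790-0.775 | 0.816 | 73 |
| 0.01 | 0.054-0.056 | 0.803-0.795 | 0.775-0.749 | 0.812-0.809 | 75-76 |
| 0.02 | 0.058-0.063 | 0.789-0.775 | 0.760-0.724 | 0.808-0.803 | 78-80 |
| 0.05 | 0.071-0.083 | 0.751-0.716 | 0.716-0.653 | 0.797-0.787 | 85-92 |
| 0.10 | 0.092-0.115 | 0.692-0.632 | 0.649-0.555 | 0.781-0.765 | 98-112 |

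By the z approximation, 75 per arm holds 80% adjusted power up to an ICC of about 0.012 (m = 8) or 0.008 (m = 12).

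**Step 6: simulation, 40,000 trials per cell.** The plain t-test rejected a true null at 0.072-0.085 for ICC 0.05 and 0.094-0.119 for ICC 0.10. A group-mean test with Satterthwaite degrees of freedom stayed at 0.050-0.054, with power 0.71-0.64 and 0.64-0.55. These agree with the table.

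**The case against.** **The harms are conditional.** A reader might infer that the trial lacks its stated 80% power and that its test runs above 5%. The document does not support either as a fact, because it gives no ICC. At ICC 0 the type I error is 0.050, and at 0.01 the departure is small. This stands, and it is why the point is put conditionally.

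**Two analyses should not be merged.** A reader might also infer that the planned t-test suffers both a large loss of power and an inflated error rate. It does not. The low power figures belong to a clustering-adjusted test that the article does not plan. The plain t-test still rejects at about 0.79 for ICC 0.05 and 0.77 for ICC 0.10 with groups of 10, but it does so with type I error above 5%. This stands.

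**Null hypothesis.** Groups are formed only for therapy. If the sessions affected nobody, they would induce no correlation and the t-test would not be inflated by it. The inflation needs group effects that vary but average zero. That is a legitimate null for a comparison of means, but it has to be stated.

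**Standardisation.** The session content is fixed, the material is to be applied in the same way in both centres, and the assessors do not run the sessions. These features may limit variation between groups. They do not establish an ICC of zero, since discussion and peer influence remain.

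**Left to a fuller plan.** The t-test sentence follows a descriptive paragraph, and random-effect structure is often left to an analysis plan. That would excuse silence. Here the article names a specific between-arm test and a complete sample-size calculation, and both assume independence.

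**Conclusion.** The point holds in conditional form. The article specifies group delivery in one arm and then fixes a sample size and a test that both ignore it. The 73 per arm is not an arithmetic error; it is correct for independent caregivers only. For any positive ICC, with effects that vary between therapy groups, the plain t-test is liberal and a valid analysis has less power than an independence calculation gives.

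The size depends on an ICC that must be assumed. Over ICCs of 0.01 to 0.10, the t-test's type I error runs from 0.054 to 0.115. Adjusted power runs from about 0.80 down to 0.56, the upper ends by z approximation and the lower ends with small-sample degrees of freedom. The consequence is therefore slight at the bottom of this range and material from about 0.05 upwards. These figures rest on a total SD of 25.7 in both arms, equal groups and complete follow-up.

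**What to change.** 1. **Data:** record a therapy-group identifier for every caregiver in the intervention arm. Without it the adjusted analysis may be impossible later.
2. **Statistical analysis section:** for the between-arm comparison, replace the independent-samples t-test with a partially nested linear mixed model. It should have a random therapy-group effect in the intervention arm only, controls as singletons, residual variance allowed to differ by arm, and Satterthwaite or Kenward-Roger degrees of freedom.
3. **Sample-size paragraph:** say that 73 per arm gives 80% power only if the ICC is 0, and show power over a stated range of assumed ICCs and the planned group size.

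The cost is one recorded variable and revised wording, a less favourable stated power and somewhat wider intervals. Keeping 150 caregivers means accepting that lower power. Restoring 80% would take about 170 to 184 in total at an ICC of 0.05, or 196 to 224 at 0.10, by the z formula; small-sample degrees of freedom would push these higher.
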